## **8.1 THE CONTROL ARM – BEST CURRENT PRACTICE**

1. **Post-CRT restaging** – The post-CRT MRI must be **performed within 4-6 weeks (no later than 10 weeks)** from completion of CRT.
2. The radiologist will be notified that the patient has been randomised into the control arm. Radiologist completes the **CONTROL ARM POST-TREATMENT MRI Form**.
3. **Surgery** is planned according to the baseline MRI and should be performed 6-12 weeks after CRT completion. A prepared **SURGERY Form** should be enclosed in the patient notes so that the surgeon can complete the form immediately after surgery.
4. A routine surgical follow up appointment will occur 4-6 weeks after surgery, therefore the **SURGICAL MORBIDITY** and **PATHOLOGY REPORTING Forms** should be completed at 6 weeks. These forms may be completed retrospectively up to 12 weeks after surgery but only complications that occur within the first 6 weeks should be recorded on the **SURGICAL MORBIDITY Form**.
5. **Adjuvant Chemotherapy** - Please complete the **CHEMOTHERAPY and TOXICITY Forms** at the end of each cycle i.e. at the end of each 3-weekly cycle of CAPOX (or single agent capecitabine) or at the end of each 2-weekly cycle of FOLFOX (or single agent 5-FU).
6. **Oncological outcomes** – 12 months from the completion of CRT please complete the **ANNUAL FOLLOW-UP Form**, and further **SURGICAL MORBIDITY** and **TOXICITY Forms** to capture late surgical complications and residual toxicity respectively. To avoid the inevitable distress caused by the relative of a dead patient receiving questionnaires, please ensure this is completed in parallel with the follow-up for Patient Reported Outcome Measures (PROMs).
7. **PROMs** – 12 months from the completion of CRT, the recruiting trial site will need to invite the patient to complete a postal questionnaire (**QUALITY OF LIFE forms**) that includes 40 questions about symptoms and quality of life. The patient will have completed the questionnaires at entry into the study and will be expecting to receive the forms. A freepost envelope addressed to the recruiting trial site will also be provided. If the patient does not initially respond please contact them by phone – to

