### 8.3 EXPERIMENTAL ARM – A ‘POOR RESPONSE’ TO CHEMORADIOOTHERAPY

1. **Post-CRT restaging** – The post-CRT MRI must be performed within 4-6 (no later than 10) weeks of completing CRT.
2. Radiologist completes the **INTERVENTION ARM POST-TREATMENT MRI Form – mrTRG 3 –5 reported.**
3. **mrTRG directed management results in the patient being offered additional chemotherapy before a decision is made regarding surgery.**
4. The option of **additional pre-operative chemotherapy** is discussed with the patient. **Chemotherapy** (Appendix 2) – The patient will receive 12 weeks (4 cycles of CAPOX or 6 cycles of FOLFOX); this should start within 12 weeks of CRT completion. Please complete the **CHEMOTHERAPY** and **TOXICITY Forms** at the end of each cycle i.e. at the end of each 3-weekly cycle of CAPOX (or single agent capecitabine) or at the end of each 2-weekly cycle of FOLFOX (or single agent 5-FU).
5. Following the completion of 12 weeks of chemotherapy a repeat MRI should be performed 4-6 weeks later and mrTRG reported. Ensure the Radiologist receives the appropriate reporting form – **INTERVENTION ARM POST-TREATMENT MRI Form** which includes the mrTRG data fields. The Radiologist completes the **INTERVENTION ARM POST-TREATMENT MRI Form**.

**mrTRG directed management results in the patient being offered deferral of surgery (if mrTRG improved to I or II) or proceeding to surgery (mrTRG remains III-V). The options of surgery or deferral of surgery as appropriate should be discussed with the patient.**

- If mrTRG now I or II and it is agreed that patient should defer surgery then patients should receive the remaining 12 weeks of chemotherapy as soon as possible following the repeat MRI and MDT meeting and be followed up in the same way as those in the ‘good-response’ sub-group described above and undergo the 5 year surveillance schedule detailed in Section 11.2.1.

- If mrTRG remains III-V then patient proceeds to surgery and undergoes the following:

6. **Surgery** is planned according to the baseline and post-treatment MRI and should be performed **6-12 weeks after pre-operative chemotherapy** is completed. A prepared **SURGERY Form** should be enclosed in the patient notes so that the surgeon can complete the form immediately after surgery.

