### 11.3 DEFINITIONS REQUIRED FOR FOLLOW-UP

**Complete response** is defined as undetectable disease at the site of the primary tumour following pre-operative chemotherapy and/or radiotherapy. A pre-fix to denote the mode of assessment must also be included - clinical (c), MRI (mr) and pathology (p).

**Disease recurrence** is defined as either evidence of loco-regional recurrence or established metastatic disease. The time to the event is measured from the start of chemoradiotherapy to the date of the diagnostic investigation or MDT.

**Regrowth** is defined as the first recorded evidence of disease at the site of the primary tumour, in a patient with previous investigations suggesting an apparent complete response or undetectable disease (mrTRG1&2). The terms 'early regrowth' and 'late regrowth' will not be used in the trial.

**Unsalvageable regrowth** is defined as a tumour with radiological evidence of a good response that is initially managed by deferral of surgery but progresses. The extent of progression means that pCRM involvement becomes inevitable and so surgery is not performed, or pCRM involvement occurs when surgery is attempted.

**Loco-regional recurrence** (one of):

- Clinical recurrence with biopsy proof of recurrence
- CEA elevation and enlarging or new mass (includes pelvic, nodal and peritoneal disease). Biopsy confirmation is contraindicated or not feasible
- CEA non-secretors: enlarging or new mass (includes pelvic, nodal and peritoneal disease). Biopsy confirmation is contraindicated or not feasible (with or without PET/CT confirmation)

**Distant Metastases** (one of):

- This is defined as any confirmed evidence of disease above the L5/S1 junction
- Clinical recurrence with biopsy proof of recurrence
- CEA elevation and evidence of distant metastases. Biopsy confirmation is contraindicated or not feasible

- CEA non-secretors: evidence of distant metastases. Biopsy confirmation is contraindicated or not feasible (with or without PET/CT confirmation). Initial report to Trials Unit should define this as SUSPECTED. A further report 6 months later should define this as CONFIRMED if supported by MDT review.

***Inoperable Disease*** (one of):

- MDT decision that the local extent of disease on the post CRT pelvic MRI is not resectable
- At laparotomy the local extent of disease is not resectable

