### 14.2.2 SECONDARY ENDPOINTS

All secondary endpoints will be summarised using descriptive statistics, and will be used to inform the design of the proposed phase III study. The following limited number of endpoints will be summarised by arm, and within arm by patients grouped by mrTRG 1-2 vs. 3-5. Exploratory comparison between arms will be carried out using Fisher's exact test for categorical variables (pCRM rate, proportion with unsalvageable regrowth, proportion of patients with any one or more grade 3-5 toxicity). Quality of surgery and surgical morbidity (maximum Clavien-Dindo grade per patient) will be compared between arms using a Mann-Whitney test. No other formal statistical comparison will be made between arms or mrTRG subgroups for endpoints not listed below.

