#### **Control arm versus Intervention arm: good responders (mrTRG1&2)**

- The pCRM involvement rate in the good responders of the control versus intervention arm
- The proportion of patients with unsalvageable regrowth (defined in section 11.3). Greater than 5% unsalvageable regrowth may lead to premature closure of the trial or decision not to proceed to the phase III study.

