## 2.2 SERIOUS ADVERSE EVENT REPORTING PROCEDURES

With one exception, serious adverse events will be collected and recorded from the date of the post-CRT MRI scan is performed until 30 days after the last dose of chemotherapy is administered.

The only exception to this rule is the recording and reporting of involved surgical resection margins described in section 2.1.4 above.

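### Unsalvageable regrowth is tested between arms although control patients cannot have it by definition, and the advisory 5% limit is listed under mrTRG1&2 although converted poor responders also defer

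*Protocol*

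**What the plan says.** **The test.** Protocol section 14.2.2 assigns exploratory comparisons between arms to Fisher's "exact test for categorical variables (pCRM rate, proportion with unsalvageable regrowth, proportion of patients with any one or more grade 3-5 toxicity"). The endpoint is then listed under the sub-heading that compares control with intervention among good responders (mrTRG1&2). There it carries a limit: "Greater than 5% unsalvageable regrowth may lead to premature closure of the trial or decision not to proceed to the phase III study".

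**The definition.** Section 11.3 says that unsalvageable regrowth "is defined as a tumour with radiological evidence of a good response that is initially managed by deferral of surgery but progresses". It has two branches: "pCRM involvement becomes inevitable and so surgery is not performed, or pCRM involvement occurs when surgery is attempted".

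**The pathways.** Under section 8.1, control-arm surgery "is planned according to the baseline MRI and should be performed 6-12 weeks after CRT completion". Section 8.3 (and the schedule in 10.3) lets an mrTRG 3-5 patient whose repeat MRI improves to I or II defer surgery, be followed like a good responder "and undergo the 5 year surveillance schedule detailed in Section 11.2.1". Section 4.2, objective 4, says that inoperable regrowth will be considered in patients managed by deferral, without an mrTRG restriction.

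**Reporting.** Appendix 1, section 2 (surgical adverse events) names unsalvageable regrowth as the sole adverse event of interest for deferral and sends it to the Adverse Event and Surveillance Forms, as does footnote d of 11.2.1. Appendix 1, 2.1.4 expedites pCRM involvement. Section 2.2 ends serious adverse event collection 30 days after the last chemotherapy dose, and adds: "The only exception to this rule is the recording and reporting of involved surgical resection margins described in section 2.1.4 above".

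**The concern.** Two things conflict. First, the comparison has no comparator: an event that exists only after deferral cannot occur in an arm with no deferral pathway. The control proportion is fixed by definition, not estimated, so a p-value against it answers no safety question. A large p-value could still be taken as reassurance.

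Second, the only numerical limit attached to the safety of deferral is tied to a group that need not contain everyone who defers. Section 14.2.2 does not say which MRI defines mrTRG1&2 for this purpose, or who forms the denominator. With groups this small, that choice alone can put the same single event above or below 5%.

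There is also a smaller reporting issue. Surveillance runs for 5 years, whereas adverse event collection closes 30 days after chemotherapy. The documents do not say clearly how a late regrowth that is never resected is to be reported.

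**Working it through.** The 5% is a fixed limit with no derivation, so there is no plan figure to reproduce.

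**Inputs.**
- Planned sample size 90 (Trial Summary) and 2:1 allocation (section 3.2): about 60 intervention and 30 control.
- Share of good responders: not given. Section 1 says that up to 30% achieve a complete or near-complete response. That is a ceiling for response in general and not an mrTRG1-2 rate. I take 30% as a working value and 20-50% as the range.
- Conversion of poor responders at the second MRI: not given. I assume 10-30%.
- All eligible patients are assumed to accept deferral. Section 8.2.1 allows them to decline.
- No alpha is stated for this comparison. I use two-sided 0.05.

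**Step 1. Fisher's test against a fixed zero.** At a 30% share the groups are 18 and 9.
- 1/18 v 0/9: p = 1.0, although 1/18 = 5.6% already exceeds 5%.
- 5/18 (28%) v 0/9: p = 0.136.
- Eight events (8/18 = 44%) are needed for p ≤ 0.05.
- With 18 v 9, the chance of p ≤ 0.05 is 0.0002 at a true rate of 10% and 0.016 at 20%.

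**Step 2. The 5% limit in the first-MRI good responders.** The smallest crossing count r is the first integer above 0.05n, and P(cross) is the binomial tail P(X ≥ r). For n = 18, r = 1, so P(cross) at 2% is 1 − 0.98^18 = 0.30.

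| Share | Intervention / control | Events to exceed 5% | Fisher p at that count | P(cross), true 2% | P(cross), true 5% | Events for p ≤ 0.05 |
|---|---|---|---|---|---|---|
| 20% | 12 / 6 | 1 | 1.0 | 0.22 | 0.46 | 7 (58%) |
| 30% | 18 / 9 | 1 | 1.0 | 0.30 | 0.60 | 8 (44%) |
| 40% | 24 / 12 | 2 | 0.54 | 0.08 | 0.34 | 8 (33%) |
| 50% | 30 / 15 | 2 | 0.55 | 0.12 | 0.45 | 8 (27%) |

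At every share the limit is crossed at a count where Fisher's test is far from significance.

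**Step 3. Precision.** With 0/18 events the two-sided exact 95% upper limit is 1 − 0.025^(1/18) = 18.5% (the one-sided 95% bound is 1 − 0.05^(1/18) = 15.3%).

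**Step 4. All deferrers.** At a 30% share, 60 − 18 = 42 are poor responders.

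| Conversion | Converters | All deferrers | One event | Two events | P(≥2), true 2% | Deferrers outside first-MRI group |
|---|---|---|---|---|---|---|
| 10% | 4 | 22 | 4.5% | 9.1% | 0.07 | 18% |
| 20% | 8 | 26 | 3.8% | 7.7% | 0.09 | 31% |
| 30% | 13 | 31 | 3.2% | 6.5% | 0.13 | 42% |

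The last probability column is 1 − 0.98^n − n × 0.02 × 0.98^(n−1). One event exceeds the limit at 1/18 and not at 1/22. The reversal is not universal: at a 20% share with 10% conversion there are 12 + 5 = 17 deferrers, and 1/17 = 5.9% still crosses.

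**Step 5. Reporting, branch by branch.**
- Margin involved at attempted surgery: this is pCRM involvement, so it is expedited under Appendix 1, 2.1.4 and exempt from the time window under 2.2.
- Surgery not performed: recorded on the two forms, due within one month (section 12.5). It is not in the 2.1.4 list or the 2.2 exception. Section 2.2.1 exempts events after the window unless they are events of special interest or causally related to trial treatment. Appendix 1 calls this event definitely related to deferral, which may bring it back in. The separate exemption for disease progression may take it out again.

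**The case against.** The comparison is labelled exploratory and the 5% limit does not depend on it, so the test itself does limited harm. That stands. It does not give the test content, and the protocol states the test explicitly, so this is not a gap left for the SAP.

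It can also be said that converters are not overlooked: section 4.2 covers all deferrals, and 14.2.2 summarises these endpoints within arm by mrTRG 1-2 and 3-5. So a converter's event would be reported descriptively. That is fair, and a reader who inferred that the denominator is definitely wrong would go too far. What can be supported is that the limit is listed under mrTRG1&2 without stating the defining MRI or the denominator.

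Other stronger readings are tempting and unsupported:
- **That the event is left out of expedited reporting.** The involved-margin branch is expedited and the unresected branch is recorded on two forms. Only the route for the latter after the window closes is unclear.
- **That crossing 5% closes the trial, or that nothing else can.** The wording is advisory. Section 13.4.2 gives the monitoring committee a wider remit, with meetings yearly or more often if considered appropriate.
- **That a crude proportion read at an unstated time is a fault of the plan.** Section 14.2.2 leaves methods and timing to a detailed analysis plan that is not at hand.
- **That 18 deferrers is the protocol's number.** It rests on an assumed share.

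**Conclusion.** The point holds in two parts. Barring off-protocol deferral in a control patient, the between-arm Fisher test compares the intervention arm with a proportion that is zero by definition. It says nothing about the 5% limit: at 18 v 9 it needs a 44% event rate for significance. The population for the limit is also not fixed to the patients at risk, and this can change the result. With 12-30 good responders, one or two events cross 5%. If converters bring the deferrers to about 22-31, two are needed. A point estimate alone would mislead in either direction, since one event in 18 crosses with probability 0.30 at a true 2% and none in 18 is compatible with 18.5%. These sizes rest on the assumed responder share, conversion rate and full acceptance of deferral. The structural zero does not. The reporting issue is an inconsistency for unresected cases only. This should be corrected, but it does not threaten the primary endpoint.

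**What to change.** 1. In section 14.2.2, delete unsalvageable regrowth from the endpoints compared between arms by Fisher's test.
2. Report it as a one-sample proportion among all intervention patients who start deferral, whether after the first or the second MRI, with an exact confidence interval.
3. State that the 5% limit applies to that denominator, and give the monitoring committee the interval beside the estimate.
4. Reconcile Appendix 1, section 2 and footnote d of 11.2.1 with Appendix 1, 2.1.4, 2.2 and 2.2.1, so that it is clear how the branch without surgery is reported once 30 days have passed since chemotherapy. The involved-margin branch needs no change.

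The cost is wording in the analysis and safety sections. The Surveillance and Adverse Event Forms already capture the event, so no new data collection is needed for the estimate.

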### **3.3 RESTAGING MRI REPORTING AND INTERVENTION ARM SUB-GROUPS**

Patients should undergo the restaging MRI 4-6 weeks (maximum of 10 weeks) following completion of their initial pre-operative CRT therapy with planned surgery in the control arm at 6-12 weeks and commencement of further consolidation therapy in the interventional arm within 12 weeks.

The radiologist will be trained to report the MRIs according to synoptic proforma reporting with specified templates:

**CONTROL ARM POST-TREATMENT MRI CRF** - there is currently a lack of surgical equipoise to change operative approach based on post treatment MRI assessment. Therefore the operative decision in the control arm will be determined by the baseline MRI. Post-operative adjuvant therapy will be offered to patients based on baseline MRI features of high risk.

**INTERVENTION ARM POST-TREATMENT MRI CRF** – synoptic reporting will be performed according to the MRI form. The MRI form for the intervention arm has an additional datafield for mrTRG reporting. The mrTRG result should be discussed at the MDT:

**For mrTRG 1&2 (good response)** - deferral of surgery should be offered to the patient, with chemotherapy offered if high risk features were present on the baseline scans.

**For mrTRG 3-5 (poor response)** – 12 weeks of consolidation therapy will be offered, followed by a restaging MRI prior to a decision regarding surgery.

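### Unsalvageable regrowth is listed for a between-arm Fisher's exact test, but the control count is zero by design, so the exploratory p-value says nothing about excess harm from deferral

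*Protocol*

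**What the plan says.** Section 14.2.2 first states that all secondary endpoints are to be described, for a limited set by arm and by mrTRG group within arm. It then adds tests: "Exploratory comparison between arms will be carried out using" Fisher's "exact test for categorical variables (pCRM rate, proportion with unsalvageable regrowth" being the second variable in the list. The bullets that follow put this endpoint under "Control arm versus Intervention arm: good responders (mrTRG1&2"): "The proportion of patients with unsalvageable regrowth (defined in section 11.3"). The same bullet says that a rate above 5% may lead to early closure or to a decision against phase III. No test is attached to that threshold.

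Section 11.3 says that unsalvageable regrowth "is defined as a tumour with radiological evidence of a good response that is initially managed by deferral of surgery but progresses". Appendix 1, section 2 treats it as the adverse event of deferral and as definitely related to it.

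The two arms are managed differently. In control, section 8.1 says that surgery "is planned according to the baseline MRI and should be performed 6-12 weeks after CRT completion"; that pathway has no deferral or surveillance step. For intervention patients graded mrTRG 1-2, section 3.3 says that "deferral of surgery should be offered to the patient, with chemotherapy offered if high risk features were present on the baseline scans".

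**The concern.** A test of equal proportions needs both groups to be able to have the event. Here one group enters the risk set only by leaving its allocated pathway. The null hypothesis would be true only if deferral never failed, which is not a clinical question about excess harm over surgery.

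Section 4 says the feasibility trial has to determine the safety of deferring surgery, and this is the outcome that speaks to it most directly. A table that sets the intervention count beside a control zero, with a large p-value, could be taken as showing no excess risk. It would show only that the groups are small.

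**Working it through.** **Inputs from the protocol.** Planned sample size 90 (Trial Summary). Allocation 2:1 (section 3.2), so 60 intervention and 30 control. Threshold 5% (section 14.2.2). The protocol gives no power or error rate for this endpoint, so there is no planned figure to reproduce.

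**Assumptions.** The share graded mrTRG 1-2 is not stated; I take 30-60% (section 1 mentions up to 30% with a complete or near complete response). Alpha for this test is not stated; I take two-sided 0.05. The control count is fixed at 0.

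**Formula.** With x events, all among n1 intervention patients, and none among n2 controls, the one-sided Fisher p-value is C(n1, x) / C(n1+n2, x). The two-sided value adds every other table with the same margins that is no more probable.

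**Just above the threshold, 24 versus 12, x = 2 (8.3%).**
- Both events in intervention: C(24,2)/C(36,2) = 276/630 = 0.438.
- One in each arm: 288/630 = 0.457, which is more probable and so not added.
- Both in control: 66/630 = 0.105, added.
- Two-sided p = 0.438 + 0.105 = 0.54.

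The 0.105 comes from tables with events in control, which the design does not allow.

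**First p<0.05, 24 versus 12, x = 8.** One-sided: 735,471/30,260,340 = 0.024. Adding the tables with 0, 1 or 2 events in intervention (495 + 19,008 + 255,024 = 274,527) gives 1,009,998/30,260,340 = 0.033.

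**All scenarios.**

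| Intervention vs control | Smallest count above 5% | p | 7 events: p | First p<0.05 | Rate / 5% |
|---|---|---|---|---|---|
| 18 vs 9 (30%) | 1/18 (5.6%) | 1.00 | 0.059 | 8/18 (44.4%), p=0.026 | 8.9 |
| 24 vs 12 (40%) | 2/24 (8.3%) | 0.54 | 0.070 | 8/24 (33.3%), p=0.033 | 6.7 |
| 30 vs 15 (50%) | 2/30 (6.7%) | 0.55 | 0.077 | 8/30 (26.7%), p=0.038 | 5.3 |
| 36 vs 18 (60%) | 2/36 (5.6%) | 0.55 | 0.082 | 8/36 (22.2%), p=0.041 | 4.4 |
| 60 vs 30 (whole arms) | 4/60 (6.7%) | 0.30 | 0.090 | 8/60 (13.3%), p=0.048 | 2.7 |

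At a true rate of 10%, twice the threshold, the chance of 8 or more events is 0.0%, 0.2%, 0.8% and 2.4% for 18, 24, 30 and 36 intervention good responders, and 25% for 60. A one-sided test at 0.05 would need 7 events in each good-responder case (19-39%) and still 8 of 60 overall.

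**What a single-group estimate shows.** Exact (Clopper-Pearson) 95% intervals: for 0/18, the upper limit is 1 - 0.025^(1/18) = 18.5%, so 0-18.5%; for 2/24, 1.0-27.0%. These show plainly how little a small group can exclude relative to 5%.

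**The case against.** The strongest reply is that little depends on this test. It is labelled exploratory. The 5% threshold acts on the observed proportion, each event is recorded individually on the adverse event form, the DMEC receives interim safety and outcome data (section 13.4.2), and section 4.2 promises specific attention to inoperable regrowth in deferred patients. All of that stands, and it limits the consequence.

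Three stronger readings are tempting, and the protocol does not support them.

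- A reader might infer that the regrowth rate read against 5% is not a planned analysis. It is: section 14.2.2 provides the description by arm and mrTRG group and states the threshold in the same bullet. Interval methods may properly be left to the SAP, so their absence here is not a fault.
- A reader might infer that a non-significant result would override the 5% rule. The protocol links no decision to the p-value.
- A reader might infer that a control patient can never have the event. The definition, "a tumour with radiological evidence of a good response that is initially managed by deferral of surgery but progresses", turns on management, not allocation. Section 2.1 notes that some centres already offer deferral, and the line in Appendix 4 on not operating when a patient is eligible for deferral is not limited by arm. An off-pathway control patient could qualify. The zero holds under the planned pathway, and a comparison that works only through deviations is not a useful one.

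It is also fair to say that the size depends on unstated inputs, and that comparing whole arms lowers the multiple to 2.7. The bullet heading points to good responders, so both are shown.

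**Conclusion.** The point holds as a fault in a stated exploratory analysis. The protocol names a between-arm test for an outcome that only deferred patients can have, so the control proportion is zero by design and the p-value carries no information on excess harm. Under the assumptions above (two-sided 0.05, 60 versus 30, 30-60% good responders, no control events), significance needs 8 events: 22-44% in good responders or 13.3% over whole arms, about 2.7 to 9 times the protocol's 5%. The sample size, the primary endpoint and the 5% rule are unaffected. What is at stake is a misleading p-value beside the key safety result for deferral, and it is worth correcting because the correction is simple.

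**What to change.** 1. In section 14.2.2, delete unsalvageable regrowth from the variables for Fisher's exact test, and take it out of the list headed as a control-versus-intervention comparison.
2. Report it as number/total among intervention patients who deferred surgery, with an exact 95% interval set against 5%. State the denominator: section 8.3 lets patients first graded mrTRG 3-5 defer if they improve to mrTRG I or II. They are at risk of the event but lie outside the initial mrTRG 1-2 group. Describe any off-protocol control deferral separately.
3. For the between-arm question on local safety, rely on pCRM involvement, which section 14.2.2 already lists for all patients and for good responders. Say that unresectable local disease counts as failure in both arms. Section 17 classes unoperated patients free of regrowth at 3 years as pCRM negative but does not classify those left unoperated because the tumour cannot be resected, so regrowth of that kind could otherwise drop out of the comparison.

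The cost is wording in section 14.2.2 and the SAP, with one added line on the pCRM endpoint. The sample size does not change, and the surveillance, pathology and adverse event forms already record regrowth and margin status.
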